#### Long-term follow-up

After EOT, all patients move to the observational follow-up with 3-monthly visits. For patients of the MRD-triggered arm, safety follow-up starts after the last visit of the last cycle of chemotherapy with subsequent transition to observational follow-up until the end of the study (EOS).

After the end of the study visit, patients are routinely followed-up and treated as per the standard of care at the discretion of the treating physician. Follow-up is planned to continue until the last patient alive has been observed for at least 2 years in total (study treatment including subsequent follow-up). Assuming 2 years of recruitment, the total observation period of the first patient may last up to 4 years. Event-free and overall-survival follow-up is recorded until the end of the overall study.

#### Additional study procedures during salvage, maintenance therapy, and follow-up

Patients undergo efficacy and safety assessments, including monitoring of Measurable Residual Disease (MRD), bone marrow specimen collection, and blood and urine sampling before receiving the study drug and at the end of each treatment cycle. During maintenance and follow-up, trial-specific samples are taken every third month. Routine examinations (physical signs, blood values, etc.) are taken at least weekly during treatment. Patient-reported outcome questionnaires are to be completed before treatment and after the end of each treatment cycle, and additionally in 3-month intervals during maintenance and follow-up. AEs are recorded during every visit. Strong CYP3A4 inhibitors should be avoided, and strong or moderate CYP3A4 inducers must not be used.

### Participants

#### Inclusion criteria

Inclusion criteria are outlined in Table 3. Key inclusion criteria are AML according to the 2016 WHO classification, relapse or refractory disease including autologous or allogeneic hematopoietic cell transplantation, positivity for FLT3-ITD mutation defined as a ratio of mutant to wild-type alleles of at least 0.05, age between 18 and 75 years, Eastern Cooperative Oncology Group (ECOG) performance status between 0 and 2, adequate renal and hepatic function, and serum electrolytes (potassium, calcium, and magnesium) within normal limits. Refractoriness to induction therapy is defined as no CR, CRi, or partial remission (PR) after one or two intensive induction cycles of at least 7 days of cytarabine 100–200mg/m^2^ continuously or an equivalent regimen with cytarabine with total dose not less than 700mg/m^2^ per cycle and 2 days of an anthracycline (e.g., daunorubicin, idarubicin). Relapse after first-line therapy is defined as relapsed AML after a first-line therapy including at least one intensive induction and consolidation therapy including allo-HCT. The discontinuation of cytotoxic agents except hydroxyurea to control hyperleukocytosis or investigational treatments for at least 10 days or 28 days respectively is mandatory. Furthermore, all patients randomized into the study must be willing to use highly effective birth control and all female patients must have a negative serum pregnancy test.

#### Exclusion criteria

Exclusion criteria are summarized in Table 3. Main exclusion criteria are diagnosis of acute promyelocytic leukemia (APL) French-American-British classification M3 or World Health Organization classification of APL with translocation t(15;17) (q22;q12), or BCR-ABL–positive leukemia. Other exclusion criteria are known active CNS leukemia, isolated extramedullary manifestation of AML, hyperleukocytosis (leukocytes > 30,000/μl), uncontrolled or significant cardiovascular disease, history of other malignancies (except adequately treated nonmelanoma skin cancer, curatively treated in situ disease, or other solid tumors curatively treated with no evidence of disease for at least 2 years), patients within the first 100 days posterior to allo-HCT, clinically relevant Graft-versus-Host-Disease, QTc interval >450 ms, or any known relevant dysrhythmias.

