Regarding dosage and schedule, in the first-in-human phase I study, CP0001, quizartinib was administered with intermittent dosing (14 days on drug followed by 14 days rest) from 12 to 450mg and continuous dosing at 200mg and 300mg for 28 days in 76 patients with r/r-AML, regardless of *FLT3*-ITD mutation status [13]. Plasma taken from subjects and assayed in an in vitro plasma inhibitory assay (PIA) showed rapid and durable inhibition of *FLT3* phosphorylation as early as 2 h after the first dose. The overall response rate was 53% in *FLT3*-ITD mutated and 14% in *FLT3*-ITD unmutated patients [13].

The response rate observed in Study CP0001 was confirmed in the phase II study, AC220-002, of single-agent quizartinib in r/r AML. In this phase II study, a total of 333 patients were enrolled in 2 cohorts; Cohort 1 included patients 60 years or older who were relapsed or refractory to the first line of therapy, and Cohort 2 included patients 18 years or older who were relapsed or refractory to salvage therapy or relapsed after allo-HCT. In Cohort 1, the composite complete remission (CRc) rate was 57% in *FLT3*-ITD mutated patients with a median survival of 25.3 weeks [20, 21]. Cohort 2 showed a CRc rate of 46% in *FLT3*-ITD mutated patients with a median survival of 24.0 weeks [20]. Notably, 35% of Cohort 2 *FLT3-*ITD mutated patients were bridged to allo-HCT [22].

The maximum tolerated dose (MTD) determined in the phase I study, CP0001, was 200mg continuous daily dosing [13]. However, in the phase II study AC220-002, 35% of patients experienced grade 3 QT prolongation at the 200mg dose, and therefore the dose was reduced. A single case of grade 4 QT prolongation, Torsades de Pointes, was reported in the AC220-002 Study in a patient with pneumonia, atrial fibrillation, taking concomitant medications known to cause QT prolongation [23]. No deaths related to QT prolongation have been reported [20].

The phase IIb 2689-CL-2004 Study was subsequently conducted. A total of 76 patients with *FLT3-*ITD-mutated AML were randomized to 60mg or 30mg quizartinib daily to examine the efficacy and toxicity at these lower doses. Both males and females were randomized to each dose. The study showed that the CRc rate was similar for both doses and to the rate observed in the earlier AC220-002 Study [24].

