### Treatments and study procedures

#### Salvage therapy

All patients are randomized upfront and receive one cycle of backbone salvage therapy with a standard HAM regimen. In patients aged 18–60 years, one cycle of cytarabine 3g/m^2^ every 12 h will be administered intravenously on days one to three, and in patients older than 60 years of age, cytarabine will be administered at a reduced dosage of 1g/m^2^ bidaily on days one to three. Mitoxantrone will be administered irrespective of age group, intravenously at a dosage of 10mg/m^2^ on days two and three. All patients will receive in addition 40 mg of quizartinib orally on days 1 to 28. If on day 28 no hematological recovery has occurred, and according to the first bone marrow examination no CR is achieved, quizartinib may be given until day 42 and a second remission control can be done if medically justified until day 42. If a therapy with a strong CYP3A4 inhibitor is initiated, a dose reduction of quizartinib to 20mg per day will be initiated. Dose modifications in case of toxicities are described in Tables 1 and 2.

**Table 1 Tab1:** Dose reduction or interruption of quizartinib

Nonhematological events grade 3 related to quizartinib and persisting > 48 h without resolution to ≤ grade 2	Dosing will be interrupted for up to 14 days. If the AE resolves to ≤ grade 1 within 14 days, the subject may resume dosing at the reduced dose of at least 50%.
Grade 4 toxicity at least possibly due to study drug	Treatment will be discontinued
Myelosuppression CRp or CRi	Dose may be reduced without interruption if the following criteria are met: Subject has received a minimum of 2 cycles of ASP2215, platelets < 25 × 10^9^/L and/or ANC ≤ 0.5 × 10^9^/L, marrow blasts < 5%, no evidence of extramedullary disease, further dose reduction is permitted if dosing 1 full cycle at the reduced dose has not resulted in the desired hematologic recovery.

*Abbreviations: AE*, adverse event; *ANC*, absolute neutrophil count; *CRi*, complete remission with incomplete hematologic recovery; *CRp*, complete remission with incomplete platelet recovery

**Table 2 Tab2:** Dose reduction or interruption of quizartinib in case of QTcF prolongation

QTcF >480 ms ≤500 ms	The dose of quizartinib will be reduced by at least 50%without interruption of dosing. Following dose reduction, the quizartinib dose may be resumed at the previous level in the next cycle if the QTcF has decreased to within 30 ms of baseline or <450 ms.

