QTcF >500 ms	Quizartinib dosing will be interrupted for up to 14 days. • If QTcF returns to within 30 ms of baseline or <450 ms within 14 days, quizartinib administration may be resumed at a reduced dose. If QTcF >500 ms occurs during the Induction or Consolidation Phases, and if no cause other than quizartinib can be identified, then during the maintenance phase, the dose of quizartinib cannot be escalated to 60 mg/day.
QTcF >500 ms or >60 ms change from baseline, and Torsade de pointes or polymorphic ventricular tachycardia or signs/symptoms of serious arrhythmia	Quizartinib dosing will be permanently discontinued.

*Abbreviations: QTcF*, corrected QT interval by Fredericia

Subjects who experience QT interval prolongation of more than 480 ms corrected for heart rate (QTcF) will undergo dose interruption and/or reduction of quizartinb and will be monitored closely by ECGs, performed twice weekly for the first week of the QTcF prolongation and then weekly thereafter until the QTcF prolongation is resolved (Table 2). QTcF prolongations higher than grade 3 according to the National Cancer Institute Common Terminology Criteria for Adverse Events (CTC AE) will be recorded as adverse events of special interest (AESI) including the Investigator’s assessment of seriousness, causality, and a detailed narrative.

In the event of significant toxicity grade 3 or 4, dosing must be interrupted, delayed, and/or reduced by at least 50% [20]. In the event of unresolved or severe toxicities, administration will be interrupted and in case of multiple toxicities, dose modification should always be based on the worst toxicity observed. Quizartinib will be discontinued in case of non-hematological grade 4 toxicities including grade 4 QTcF prolongation.

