Comorbidities	- Adequate renal function defined as creatinine clearance >50 mL/min (calculated using the standard method for the institution)	- Inadequate renal function. - Inadequate liver function. - Known liver cirrhosis. - History of Sinusoidal Obstruction Syndrome (SOS) - Uncontrolled hypertension. - Severe obstructive restrictive. ventilation disorder. - Myocardial infarction. - Congenital long QT syndrome. - Torsades de pointes. - Arrhythmias (including sustained ventricular tachyarrhythmia). - Right or left bundle branch block and bifascicular block. - Unstable angina. - Coronary/peripheral artery bypass graft. - symptomatic congestive heart failure (NYHA III/IV). - Cerebrovascular accident. - transient ischemic attack. - Symptomatic pulmonary. embolism. - Bradycardia defined as <50 bpms. - QTc interval >470 ms. - Uncontrolled infection. - Evidence or history of severe non-leukemia-associated bleeding diathesis or coagulopathy. - Patients with a “currently active” second malignancy other than non-melanoma skin cancer. - Severe neurologic or psychiatric disorder interfering with ability of giving informed consent.
Others	- Signed written informed consent. - Ability of patient to understand the character and consequences of the clinical trial.	- No consent for biobanking. - History of hypersensitivity to the investigational medicinal product or to any drug with similar chemical structure. - Participation in a clinical study involving an investigational drugs. - No consent for registration, storage, and processing of the individual disease characteristics.

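### The QTc exclusion limit is 450 ms in the text but 470 ms in Table 3, and under the Table 3 limit Table 2's recovery condition can be met inside its own dose-reduction band

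*Protocol article*

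**What the plan says.** Four statements in the protocol article bear on this point.

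- **Exclusion criteria, running text.** The section opens by saying "Exclusion criteria are summarized in Table 3". Among the main exclusions it then lists "QTc interval >450 ms, or any known relevant dysrhythmias".
- **Table 3, Comorbidities row, exclusion column** (printed under Continuation therapy). The same criterion reads "QTc interval >470 ms".
- **Table 2** (printed under Salvage therapy). For "QTcF >480 ms ≤500 ms" the dose is reduced without interruption. It may then be "resumed at the previous level in the next cycle if the QTcF has decreased to within 30 ms of baseline or <450 ms". The row for QTcF above 500 ms uses the same recovery condition after an interruption, but allows dosing to restart only at a reduced dose.
- **Salvage therapy, text after Table 2.** Any patient whose QTcF exceeds 480 ms is to have quizartinib interrupted, reduced or both, with close ECG monitoring until the prolongation resolves.

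Both eligibility statements say QTc and name no correction formula. Table 2 and the text after it use QTcF.

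**The concern.** The text presents Table 3 as the summary of the criteria it goes on to describe, so the two QTc limits should agree, and they do not. The article offers no reading under which both could be right, such as a different limit by sex, by correction formula or by treatment phase.

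The criterion is a safety threshold for a drug that prolongs the QT interval. The Background reports grade 3 QT prolongation in 35% of patients at 200 mg in an earlier phase II study, which led to a lower dose. That figure shows the kind of risk and is not an expected rate here, because this trial starts at 40 mg and goes up to 60 mg in maintenance. Every patient in the trial receives quizartinib during salvage therapy, so the limit applies to the whole study population.

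The eligibility limit also caps the baseline that enters Table 2. Recovery there is partly defined relative to baseline, so a higher permitted baseline raises the QTcF at which a patient counts as recovered. Whether Table 2 agrees with itself depends on which limit is in force.

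**Working it through.** The article gives no figure to reproduce. The check compares stated limits.

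**Inputs**

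| Quantity | Value | Place |
|---|---|---|
| Exclusion limit, text | QTc above 450 ms | Exclusion criteria |
| Exclusion limit, table | QTc above 470 ms | Table 3 |
| Reduction band | QTcF above 480 and up to 500 ms | Table 2, first row |
| Recovery condition | within 30 ms of baseline, or below 450 ms | Table 2, both recovery rows |
| Text rule | QTcF above 480 ms leads to interruption and/or reduction | Salvage therapy |

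**Assumptions.** QTc at eligibility and QTcF in Table 2 use the same correction. The baseline in Table 2 is subject to the eligibility limit. QTc is recorded in whole milliseconds, and a difference of exactly 30 ms counts as within 30 ms.

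**Step 1: eligibility.** The limits differ by 470 − 450 = 20 ms. Patients with a baseline of 451 to 470 ms are excluded by the text and not excluded by Table 3.

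**Step 2: highest QTcF that counts as recovered.** The two recovery conditions are joined by *or*, so either is enough. The one fixed below 450 ms can never fall in the reduction band. For the baseline-relative one, ceiling = baseline + 30 ms.

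- Text limit, highest baseline 450 ms: 450 + 30 = 480 ms. The band starts above 480 ms, so there is no overlap.
- Table 3 limit, highest baseline 470 ms: 470 + 30 = 500 ms. At this baseline the whole band counts as recovered.
- Baselines in between: 451 + 30 = 481 ms up to 470 + 30 = 500 ms. Every baseline from 451 to 470 ms gives some overlap.

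**Step 3: an example.** Take a baseline of 465 ms, so the ceiling is 465 + 30 = 495 ms. Suppose QTcF falls from 499 to 490 ms. Then 490 − 465 = 25 ms, which meets the recovery condition and permits the previous dose level in the next cycle. But 490 ms is above 480 ms, so the same reading is still in the reduction band and still falls under the text rule.

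**Step 4: the row above 500 ms.** The same overlap arises, but dosing there restarts only at a reduced dose. The conflict is therefore milder than in the first row, where the previous level may return.

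**The case against.** The two limits contradict each other on any reading. The case on the other side concerns how far the consequences go, and much of it stands.

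- **The Table 2 clash is conditional.** It cannot arise under the limit in the text. It also needs the same correction in eligibility and in Table 2, which the article does not state. Both conditions are accepted and limit the second half of the point.
- **Resumption is optional.** Table 2 says the dose *may* be resumed, whereas the text rule above 480 ms is mandatory. This is a conflict of wording. It does not show that any patient would return to the previous dose at such a value.
- **Divergent enrolment is an inference.** A reader might conclude that sites enrolled populations with different cardiac risk. The article does not support that: sites work from the full protocol, which is not shown and may state one limit throughout.
- **The practical reach is small.** Trial status reports 11 patients and a decision to close early. An amendment to eligibility would change little in conduct.

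A reader might also infer that the rule making "QTcF prolongations higher than grade 3" adverse events of special interest is a mistake, because it omits grade 3 and the Background reports only one grade 4 case. The documents do not support this. No other place sets a different threshold, so there is nothing to contradict it. Nor would grade 3 events go unrecorded: Safety assessments documents all adverse events after screening, and adverse events are recorded at every visit. At most the special-interest flag and its narrative are lost. The earlier study's 35% and single grade 4 case cannot be used to size that loss, because the 35% refers to 200 mg and the number of patients at that dose is not given.

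**Conclusion.** The QTc exclusion limit is wrong as written in one of its two places. The article does not show which place. The contradiction covers baselines of 451 to 470 ms and rests on no assumption beyond the article's own statement that Table 3 summarizes the criteria.

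The Table 2 conflict holds in a narrower form. If the Table 3 limit is in force, and with the same correction formula, the recovery condition can be met at 481 to 500 ms, inside the reduction band and against the text rule for QTcF above 480 ms. At a baseline of 450 ms or less it cannot occur.

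Severity is below must-fix: the trial closed early with 11 patients, and no effect on the primary endpoint or its analysis is claimed. The point still matters for the published record of a safety criterion.

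**What to change.** 1. Check the Exclusion criteria text and Table 3 against the full protocol. State one QTc limit in both places, with its correction formula.
2. Confirm which limit was applied to the 11 enrolled patients, and report it with the trial results.
3. Reconcile the recovery wording in Table 2 with the rule for QTcF above 480 ms in Table 2 and in the Salvage therapy text.

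Which limit and which dosing rule apply is for those responsible for the protocol to settle; none is proposed here. The cost is a wording correction and a check of the eligibility records of 11 patients. The design, sample size and analysis do not change.

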### Efficacy endpoints

The primary endpoint of the study is the achievement of CR, Cri, or CRh after salvage therapy with HAM in combination with quizartinib. CR is defined as bone marrow blasts <5%, absence of circulating blasts and blasts with Auer rods, absence of extramedullary disease, neutrophil count ≥1000/μl, and platelet count ≥100,000/μl. CRi is defined as CR with residual neutropenia (neutrophils < 1000/μl) or thrombocytopenia (platelets < 100 000/μl) and CRh is defined as a CR with partial recovery of peripheral blood counts with residual neutropenia (neutrophils < 500/μl) or thrombocytopenia (platelets < 50,000/μl).

Refractory disease or treatment failure is defined as failure to achieve CR, Cri, or CRh, presence of Auer rods, or appearance of new or worsening extramedullary disease after one course of intensive treatment. Relapse after CR, CRi, or CRh is characterized by ≥5% blasts in the bone marrow aspirate and/or biopsy not attributable to any other cause, the reappearance of leukemic blasts in the peripheral blood, the new appearance of extramedullary leukemia, or presence of Auer rods. Platelet and neutrophil counts for the assessments of CR, CRi, and CRh are delineated based on the 2017 recommendations from the International Working Group commissioned by the European Leukemia Net [26].

Secondary survival endpoints are event-free survival (EFS), defined from randomization until one of the following events, whichever occurs first: (a) failure to obtain CR or CRi or CRh after Q-HAM therapy, (b) relapse from CR/Cri/CRh, or (c) death from any cause. Patients without an event are censored at the last follow-up. Overall survival (OS) is defined as the time from randomization until death from any cause and relapse-free survival (RFS) is measured from the first CR/Cri/CRh to the time of recurrence of the disease or death from any cause, whichever occurs first. Patients without event are censored at the last date of follow-up. Cumulative incidence of relapse (CIR) is defined as the time from the achievement of a CR/CRi/CRh after salvage therapy to the recurrence of the disease, whereby death from any cause is a competing event. Cumulative incidence of death (CID) is defined as the time from the achievement of a CR/CRi/CRh after salvage therapy to death from any cause whereby recurrence of the disease is a competing event.

Further secondary endpoints are patient-reported outcomes (PROs). PROs include assessments of (a) health-related quality of life (QoL), calculated as the EORTC QLQ-C30 Summary Score [27]; (b) the quality of sleep or sleep disorders, calculated with the “Sleep Quality Index” from the PSQI according to the corresponding scoring guidelines [28]; and (c) anxiety and depression, calculated from the PHQ-4 according to the corresponding scoring manual [29].

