Common adverse events (AEs) observed in the phase I and II studies included gastrointestinal disorders (nausea, diarrhea, and vomiting), hematologic disorders (anemia, neutropenia, and thrombocytopenia), febrile neutropenia, fatigue, and QT prolongation.

Although hematologic toxicity is associated with the underlying disease, safety reports from Study AC220-002 in AML indicate delayed recovery or continued suppression of absolute neutrophil counts (ANC) and platelets as a consequence of continued treatment with quizartinib [20].

Based on phase I and phase II studies’ results, it appears reasonable and clinically feasible to combine salvage therapy with quizartinib in patients with r/r- *FLT3*-ITD mutated AML. This manuscript describes the rationale, design, and dosing details of the Q-HAM study (clinicaltrials.gov identifier NCT03989713; EudraCT No 2018-002675-17), a phase II study comparing quizartinib adjunct to salvage therapy to historical controls based on the matched threshold crossing approach.

The primary objectives of the study are (i) to assess the clinical efficacy of quizartinib in combination with high-dose cytarabine and mitoxantrone and (ii) to assess the clinical efficacy of MRD-triggered and preemptive quizartinib continuation therapy in patients with r/r- *FLT3*-ITD mutated AML.

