### Study setting and randomization

In Germany, patients with r/r-AML are usually referred to academic hospitals. Patients under treatment in the participating centers will be asked to participate in the study. Recruitment will take place in up to 20 academic centers registered in the Study Alliance Leukemia (SAL) group (http://www.sal-aml.org/). During the study conduct, participating centers (see Additional file 2) are contacted by study monitors and the medical coordinator monthly to promote patient recruitment. Furthermore, after protocol amendments or upon relevant updates during the study, a newsletter will be sent to all participating centers. Conferences with the participating centers of the SAL network are held regularly to share information regarding therapy responses and complications seen within the study. Expecting at least 5 potentially eligible patients per year and center, approximately 2 years are required to recruit the anticipated number of patients, when accounting for a consecutive study center initiation and non-participation.

Patients have to provide written informed consent and must meet all inclusion criteria before any protocol-specific procedures are performed.

Each patient must be registered in the electronic case report form (eCRF). During registration, a unique patient ID (PAT-ID) is assigned. Following registration, all eligible patients are upfront 1:1 randomized. The randomization step is triggered by the study sites using a centralized web-based tool (randomizer.at) configured by the responsible data management team. Randomization is performed stratified according to previous treatment with midostaurin. Forty patients are allocated to each arm. Twenty or more centers are selected to recruit the intended number of patients. The treatment arms are (a) the MRD-triggered arm and (b) the prophylactic arm.

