For the analysis of the primary endpoint, a logistic regression model will be applied to assess the odds ratio of CR/CRi/CRh rate after salvage therapy for patients receiving Q-HAM versus matched controls not receiving Q-HAM. The null hypothesis H0: OR≤1 is tested against its alternative H1: OR>1 at a one-sided significance level of *α*=0.05. The logistic regression analysis will be adjusted for age, high-risk cytogenetics (yes/no), and CR1 duration <18 months (yes/no/not applicable due to refractory disease). Due to the adaptive nature of the trial, two separate logistic models will be fitted for the two trial stages and be combined using the inverse normal function approach. Determination of *p*-values, point, and interval estimates will take the adaptive nature of the trial into account. Concerning the secondary endpoints: EFS, OS, and RFS endpoints will be analyzed using a Cox regression model and Kaplan-Meier plots, CIR, and CID will be analyzed according to Gray 1988 [33] and via cumulative incidence plots, and quality of life will be analyzed descriptively according to the corresponding guidelines and EORTC recommendations. Safety endpoints will be analyzed descriptively. Analyses of the primary and secondary endpoints will be based on the full analysis population (all randomized patients with treatment groups assigned in accordance with the randomization, regardless of the treatment actually received (intention to treat (ITT)). For patients with incomplete follow-up, time to last follow-up date will be used as the censoring time in the analysis of time-to-event data. Otherwise, no imputation of missing data will be conducted. For the biometricians, patient treatment shall remain blinded from the time of randomization until the final database lock. The interim analysis and sample size recalculation will be conducted by an independent biometrician who is not involved in the conduct of the trial. Statistical analysis will be performed using SAS v9.4 or higher [34].

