One of the current challenges in AML treatment is finding effective and well-tolerated post-remission therapies to produce lasting or permanent remissions after achieving a CR since this could lead to a reduction in relapse that is known to be significantly high in this group of patients. Regarding the use and efficacy of maintenance therapy with *FLT3* inhibitors, a recent publication reported the results of the European Group for Blood and Marrow Transplantation (EBMT) registry-based study, which included 462 patients with *FLT3* mutated AML. Sixty-two patients received posttransplant sorafenib: 19 prophylactic, 9 as preemptive therapy, and 34 as a treatment for relapse [43]. The multivariate analysis showed that maintenance with sorafenib significantly improved relapse-free survival (HR= 0.44 [95% CI 0.26–0.75; *p*=0.001). A preplanned pair-matched analysis was performed on data from 26 patients in the sorafenib maintenance group and 26 controls. After a median follow-up of 39 months, the 2-year leukemia-free survival (LFS) and OS were 79% and 83% in the sorafenib group, and 54% and 62% in the control group (*p*=0.002 and 0.007, respectively) [42].

Thus, the second objective of this study is to compare in a randomized manner the efficacy of prophylactic quizartinib therapy to MRD-triggered preemptive continuation therapy with quizartinib in terms of event-free survival. To our knowledge, no study so far has evaluated prophylactic maintenance with quizartinib vs. MRD-triggered continuation quizartinib-therapy.

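### EFS from upfront randomization is the named endpoint for the prophylactic versus MRD-triggered comparison, although about half of its events occur before the arms differ; RFS among responders should lead

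*Protocol article*

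**What the plan says.** The randomized question is prominent. The Background lists, as the second of two primary objectives, "to assess the clinical efficacy of MRD-triggered and preemptive quizartinib continuation therapy". The Discussion says that "the second objective of this study is to compare in a randomized manner" the two strategies, and names the endpoint: "with quizartinib in terms of event-free survival".

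Efficacy endpoints starts EFS at randomization and counts three events: "a) failure to obtain CR or CRi or CRh after Q-HAM therapy", relapse, and death. The same section starts RFS at first CR/CRi/CRh, and defines the cumulative incidences of relapse and death from remission too.

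Treatment is common to both arms at first: "All patients are randomized upfront and receive one cycle of backbone salvage therapy", with the same quizartinib added (Salvage therapy). Continuation therapy splits the arms only among patients in remission. Withdrawal of patients removes those who do not reach CR/CRi/CRh after salvage.

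Sample size calculation and statistics analyses primary and secondary endpoints in all randomized patients, and says "EFS, OS, and RFS endpoints will be analyzed using a Cox regression model and Kaplan-Meier plots". It gives no hazard ratio, event number, significance level or power for the randomized contrast.

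**The concern.** A salvage failure occurs under treatment that is the same in both arms, and the patient then leaves before either strategy starts. Such events have an expected hazard ratio of 1 whatever the strategies do. Mixing them with the relapses and deaths that the strategies can affect gives an average effect closer to 1.

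At stake is the reading of the one randomized question in the trial. A worthwhile difference between the strategies would look smaller on EFS than it is, and would more often be missed.

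**Working it through.** **No planned figure to reproduce.** The minimum of 60 patients belongs to the remission endpoint against historical controls and does not bear on this contrast.

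**Events that the strategy cannot affect.** Inputs from the article: at most 80 patients, 40 per arm, planned remission rate 0.55.

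- Salvage failures: (1 − 0.55) × 80 = 36, about 18 per arm.
- Patients who inform the strategies: 0.55 × 80 = 44, about 22 per arm.
- At other remission rates the failures are 56 (rate 0.30, the historical-control assumption), 44 (0.45) and 28 (0.65).

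**Effect on hazard ratio and power, by simulation.** From the article: 40 per arm, 55% remission, follow-up of 24 to 48 months, negligible loss. Assumed: exponential RFS with a median of 6 to 12 months in the MRD-triggered arm, a constant hazard ratio after remission, two-sided 0.05 log-rank test. Salvage failures are dated either individually between days 28 and 42 or all at 1.2 months. At a hazard ratio of 0.50 there are about 69 to 76 EFS events and 32 to 40 RFS events, so salvage failures are about 47% to 53% of EFS events.

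| True HR after remission | EFS HR (Cox) | EFS power, failures dated individually | EFS power, failures on one date | RFS HR | RFS power |
|---|---|---|---|---|---|
| 0.50 | 0.69–0.73 | 24–33% | 32–41% | about 0.50 | 47–60% |
| 0.60 | 0.76–0.79 | 17–22% | 21–27% | about 0.60 | 31–38% |
| 0.70 | 0.82–0.84 | 10–13% | 13–17% | about 0.70 | 18–24% |

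Ranges run over the medians and repeated runs. At a true hazard ratio of 0.50, a one-step log-rank estimate with all failures on one date gives 0.63 to 0.65 for EFS instead. The article names a Cox model, so 0.69 to 0.73 is the more relevant range.

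**Hand check** (HR 0.50, median 9 months: about 72 EFS and 36 RFS events; simulated standard errors of the log hazard ratio 0.24 and 0.35).

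- EFS: |ln 0.71| / 0.24 = 0.342 / 0.24 = 1.43; power ≈ Φ(1.43 − 1.96) = 0.30.
- RFS: |ln 0.50| / 0.35 = 0.693 / 0.35 = 1.98; power ≈ Φ(1.98 − 1.96) = 0.51.

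EFS has the smaller standard error, as 2/√72 = 0.24 against 2/√36 = 0.33 also suggests. The loss comes from the smaller effect.

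**Type I error.** With a true hazard ratio of 1, the EFS test rejected in 4.6% to 5.7% of simulated trials.

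**Adequacy of RFS.** Events for 80% power at two-sided 0.05: 4 × (1.96 + 0.84)² / (ln HR)². This gives 66 at HR 0.50, 121 at 0.60 and 247 at 0.70, against about 32 to 42 expected.

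**The case against.** **EFS in all randomized patients is a legitimate estimand.** It involves no selection after randomization. Restricting to responders is safe only if response does not depend on arm. Treatment is the same until then, but the trial is open-label with the arm known from the start, and Salvage therapy leaves room for judgement: a second remission assessment is possible up to day 42. Knowledge of the arm could therefore influence who is called a responder. This stands as the main cost of the fix and is the reason to keep EFS.

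**RFS is already planned.** It is defined and gets the same Cox and Kaplan-Meier analysis as EFS. Only one Discussion sentence links the contrast to EFS, and the Methods rank none of the secondary endpoints. This also stands: the point is which endpoint leads. A reader might infer that the plan has no undiluted analysis; it has one.

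**The gain rests on assumed inputs.** MRD-positive patients in the MRD-triggered arm move to quizartinib, so a hazard ratio of 0.50 may be optimistic, and at 0.70 neither endpoint has useful power. This limits the size of the benefit, not its direction.

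**The trial closed early with 11 patients.** At 55% remission that is about 6 responders (11 × 0.55 = 6.05). What remains is how the randomized data are described.

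A reader might also infer a defect from the absence of prior midostaurin in the Cox sentence, given "Randomization is performed stratified according to previous treatment with midostaurin". The documents do not support that: one condensed line names no covariates for any secondary endpoint, and an article may leave strata to the analysis plan.

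**Conclusion.** The point holds as a poor choice of lead endpoint among those already defined. At the planned remission rate, 36 of 80 patients, about half of all expected EFS events, add events unrelated to the strategies. Under the assumptions above, leading with EFS costs roughly 16 to 27 percentage points of power at a true hazard ratio of 0.50, and less at weaker effects. The count of 36 rests on a rate of 0.55 that the article chose as clinically relevant rather than as a forecast; a lower rate makes the dilution worse.

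Two stronger readings are not supported. The extra events do not make the hazard ratio less precise and do not cause false-positive findings. Nor would RFS make the comparison adequately powered: even at a hazard ratio of 0.50 it needs 66 events and would have about 32 to 40.

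**What to change.** State that the prophylactic versus MRD-triggered comparison is led by RFS from first CR/CRi/CRh, among responders, by randomized arm. Keep EFS from randomization in all randomized patients as the supportive analysis. Present the comparison as estimation, with a hazard ratio and confidence interval, rather than as a test.

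Because assessment is open-label and can be extended, report the response rate, the timing of the remission assessment and responders' baseline characteristics by arm.

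The cost is wording in the protocol or analysis plan; RFS is already defined and analysed, so no new data are needed. The price is a smaller, post-randomization analysis set whose comparability rests on response being assessed alike in both arms. Given early closure, the same ordering should be used when results are reported, with no claim about which strategy is better.
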